### *Workload*

For assessment of workload we will use the National Aeronautics and Space Administration task load index (NASA-TLX). This scoring system includes 6 scales on how an individual experiences work demands in various dimensions: Mental Demand (MD), Physical Demand (PD) and Temporal Demand (TD), Frustration (FR), Effort (EF), and Performance (PE) (Appendix 3). This self-assessment scoring system has been used more than 300 studies and used in various industries like aviation, defence and recently in health care. Reliability and validity of NASA-TLX has been demonstrated in studies. We will use raw scores of NASA-TLX rather than weighted scores as raw score is more time efficient and simpler to apply. After completing each simulation, participants would be asked to complete NASA-TLX forms. In this form, there would be definitions for each rating scale and for each domain. For each of the six domains the participants would mark their feeling in the scale of 1 to 20, in each domain. 20 being the worst experience and 1 being the best experience

## **Outcomes: Data**

### *Participants*

Participant gender and age will be recorded. Additionally, data pertaining to participant professional training and neonatal experience will also be gathered prior to the simulation, Table S1.

*Table S1: Participant data*

|                                                             | Nurses | Team leader | Doctors |
|-------------------------------------------------------------|--------|-------------|---------|
| Training / Nurse band (level)                               |        |             |         |
| Neonatal experience (years)                                 |        |             |         |
| Times completed NLS course (number)                         |        |             |         |
| Completed NLS within last 1 year (yes/no)                   |        |             |         |
| Prior neonatal simulation experiences (number)              |        |             |         |
| Prior neonatal resuscitation real life experiences (number) |        |             |         |

### *Visual attention*

During each simulation participant visual attention will be objectively assessed with a wearable eye-tracker, as previously described.

*Table S2: Visual attention outcomes*

|                                        | All scenarios
(Between participant comparison) |        |        | Within team post comparison
(Same person comparison) |        |        |
|----------------------------------------|---------------------------------------------------|--------|--------|---------------------------------------------------------|--------|--------|
|                                        | Nurse                                             | Tier-1 | Tier-2 | Nurse                                                   | Tier-1 | Tier-2 |
| AOI (description)                      |                                                   |        |        |                                                         |        |        |
| Time on AOI (seconds)                  |                                                   |        |        |                                                         |        |        |
| Time-to-first fixation (seconds)       |                                                   |        |        |                                                         |        |        |
| Saccades (mean and variability)        |                                                   |        |        |                                                         |        |        |
| Fixations (mean and variability)       |                                                   |        |        |                                                         |        |        |
| Smooth pursuits (mean and variability) |                                                   |        |        |                                                         |        |        |

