## **Outcomes: Assessment**

### *Visual attention (situation awareness)*

Will be conducted with the wearable eye tracker (Pupil Labs, Core Eye Tracker, Berlin, Germany. 160×51mm, high speed 120Hz and 200Hz, <https://pupil-labs.com/products/core>). This wearable eye-tracker is modular, easy to clean (disinfect), durable, lightweight, and ergonomically designed for safe use and deployment in any settings. It is fully mobile as it connects to a smartphone for data capture ensuring the wearer is free to move and their normal movement activity are not restricted. Data is wirelessly transferred to Pupil Labs proprietary software and stored locally. Data will then be stored on a secure server where further analysis of those data will be made using a custom-made MATLAB® (MathWorks Inc, Massachusetts, USA) algorithm

From all the simulation eye-tracking videos, the following will be analysed:

- i. Descriptors pertaining to AOI on: the baby, monitors (e.g., examining pulse oximeter), pressures on the T-piece resuscitation device (*neopuff*), mask technique, oxygen administration, endotracheal intubation (if applicable), performance of procedures like umbilical vein catheterisation, team members, and timer on the resuscitaire.
- ii. Time spent on each AOI (indicating VA distribution).
- iii. Three eye movements including fixations, saccades and smooth pursuits.

Analysis of eye tracking videos will be performed by the research team. However, one of the limitations of eye tracking is that it does not capture the situations of “Inattentional blindness”. Meaning the operator may be looking at some aspect without putting their mind to it. This will be studied by using having an additional camera in the room to gather more (situational) detail in context.

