## **Simulation**

Prior to each simulation, participants will receive briefing about features of simulation dolls (i.e., to mimic the patient), how they need to assess the doll, and what information they need to obtain from the simulation instructors. Before each scenario each team will have approximately five minutes to prepare for the simulation. We will have two scenarios, one with management of an extreme preterm infant and another with the management of a term newborn with complications at delivery. Details of term and preterm resuscitation scenarios are provided in Appendix-1 and Appendix-2. Both these scenarios were used previously in our neonatal unit simulations. Both the simulation scenarios will need endotracheal intubation with the term baby scenario needing chest compression and umbilical vein administration of epinephrine. We will use the SimNewB (Laerdal Medical, Laerdal, Stavanger, Norway) low

HUFIN\_V5\_March 2022 IRAS: 314695 10

fidelity manikin for term and Premature infant Anne-low fidelity (Laerdal Medical, Laerdal, Stavanger, Norway) for the preterm scenarios, respectively. The two scenarios will be the same for all participants. We will run the two simulation scenarios with three different teams, giving a total of 6 scenarios. Each scenario will be running approximately for 10-15 minutes.

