## **Study algorithm**

Each team will participate in two simulation scenarios (i) term and (ii) preterm. With 3 teams, there will be total of 6 simulation experiments. Each team will undergo one scenario with a team leader and another scenario without a team leader. The sequence in which each team is allocated with/without team leader would be alternating with each team. For example, if team #1 starts with team leader for their preterm scenario, team #2 would participate same preterm scenario without team leader. This will ensure that both scenarios have an equal number of scenarios with and without a team leader.

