## Sample size

In a previous study using eye tracking glasses examining VA during neonatal resuscitation, in which the operator acted both as an airway manager and team leader. In this study operator spent 35% (SD 8) of time focused on the infant. With the presence of dedicated resuscitation leader, to improve the VA on the infant to 55% with 80% power and alpha error of 0.05, we will need to conduct 6 scenarios with 3 samples in each group (equalling 18 participants).

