## Statistics

This is an exploratory study consisting of XXX groups. To the authors knowledge, there has yet to be a comprehensive analysis of VA with eye-tracking in neonatal simulations examining impact of a team lead with a checklist. However, there has been a pilot study using eye-tracking in neonatal resuscitation which used a dataset of 6 participant video-based eye-tracking recordings of 5mins duration. Therefore, our anticipated dataset size of 24 participants, will provide greater insight to examine VA behaviour differences and detect impact of a team lead with a standardised checklist. Data will be analysed in SPSS (v23, IBM) and R studio (R. RStudio, Boston, MA, USA). To conform to the exploratory nature of the work, descriptive statistics such as means, and ranges will be used here based on the number of participants stratified across 4 teams. Independent t-tests will further explore any observable differences. Those data will be complimented with simple plots. Anonymised data will be made available on reasonable request.

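### Table S2 tabulates attention in seconds, although the study is sized on percent of time and run length is not fixed, so differences in run length enter the comparison

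*Protocol*

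**What the plan says.** Four places in the protocol bear on this.

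- **Visual attention, Table S2.** The row for the measure reads "Time on AOI (seconds". It is to be filled both between participants across all scenarios and for the same person within a team. No denominator is given.
- **Visual attention (situation awareness).** The measure is described as "Time spent on each AOI (indicating VA distribution", so it is meant to show how attention is spread over the areas of interest.
- **Sample size.** The planning value is a share: "In this study operator spent 35% (SD 8) of time focused on the infant". The target is "to improve the VA on the infant to 55% with 80% power and alpha error of 0.05", from which the protocol concludes "we will need to conduct 6 scenarios with 3 samples in each group (equalling 18 participants".
- **Simulation.** Run length is given as a range: "Each scenario will be running approximately for 10-15 minutes".

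The Study algorithm section adds that "Each team will undergo one scenario with a team leader and another scenario without a team leader", with three teams and alternating allocation. The Statistics section plans descriptive summaries, after which "Independent t-tests will further explore any observable differences".

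**The concern.** The protocol plans on one scale and tabulates on another. A share of time does not depend on how long the run lasted, whereas seconds do. The stated range allows the longest run to be 1.5 times the shortest, and the effect sought is a ratio of 55/35 = 1.57. The permitted variation in length is therefore almost as large, in relative terms, as the whole effect.

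This would matter little if length were unrelated to leader status, but the design links them in two ways. Every same-person comparison sets a term run against a preterm run. With three teams, each scenario is run three times, so it cannot be split equally between led and unled runs; one condition has two term runs and one preterm, the other the reverse. Only the term scenario is described as needing chest compressions and umbilical venous drug administration, so unequal lengths are plausible, though not stated.

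At stake is whether a difference in the table reflects where the operator looked or how long the run was. A result in seconds also cannot be set directly against the 35% to 55% assumption.

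**Working it through.** **Inputs.** Share on the infant 35% without and 55% with a leader, SD 8 points, alpha 0.05, power 80%, 3 per group (Sample size). Run length 10 to 15 min, i.e. 600 to 900 s (Simulation). Three teams, each led in one scenario and not in the other (Study algorithm). Two-sided testing is assumed because sidedness is not stated.

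**Step 1: the plan's own figure.** By the normal approximation, n per group = 2 × [8 × (1.960 + 0.842) / 20]² = 2.51, rounded up to 3. The stated 3 per group is reproduced, on the percent scale. A two-sided t-test with 3 per group has 64% power. That shortfall is a separate matter; 64% serves here only as the baseline for the simulations below.

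**Step 2: shares turned into seconds** (share × minutes × 60).

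| Run length | 35% | 55% | Difference |
|---|---|---|---|
| 10 min | 210 s | 330 s | 120 s |
| 12.5 min | 262.5 s | 412.5 s | 150 s |
| 15 min | 315 s | 495 s | 180 s |

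At equal run lengths a true 20-point effect is worth 120 to 180 s.

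**Step 3: length tied to scenario.** Assume term runs of 15 min, preterm runs of 10 min and a true 20-point effect for every team.

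- A team led in the preterm run: 330 − 315 = 15 s.
- A team led in the term run: 495 − 210 = 285 s.
- Two teams led in preterm, one in term: (330 + 330 + 495)/3 = 385 s against (315 + 315 + 210)/3 = 280 s, a difference of 105 s.
- Two teams led in term, one in preterm: (495 + 495 + 330)/3 = 440 s against (210 + 210 + 315)/3 = 245 s, a difference of 195 s.
- No true effect, 35% throughout: the 2:1 split alone gives 280 − 245 = 35 s.

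In the 105 s case, a simulation of independent t-tests on seconds (3 per group, SD 8 points of run time, 200,000 replicates) rejected in about 7% of replicates. The contrast is smaller, and mixing long and short runs in one group widens the spread.

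**Step 4: worst case, length tied wholly to leader status.**

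- Led runs 10 min, unled 15 min, true 20-point effect: 330 − 315 = 15 s. Simulated rejection falls from 64% at equal lengths to 6%.
- No effect, 35% in both, 15 against 10 min: 315 − 210 = 105 s. Simulated rejection is 37%.

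**Step 5: length random and unrelated to leader status** (uniform on 10 to 15 min). The mean difference stays at 150 s under the planned effect and at 0 under no effect, so there is no bias. Simulated power falls from 64% to 48%.

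**Step 6: the same data as a percentage of run time.** The contrast is 55 − 35 = 20 points in every case above, whatever the run lengths.

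**The case against.** The strongest reply is that Table S2 is an empty shell listing what will be gathered, that seconds are the natural output of an eye-tracker, and that deriving a percentage can be left to the statistical analysis plan. The percent figures in the sample size, and the stated purpose of showing a distribution, make the intent visible. This explains how the mismatch arose but does not remove it. The protocol does not stay silent on the unit: it states one, and that unit conflicts with its own planning scale.

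Several other points stand and limit the concern.

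- No section says that a leader shortens runs or that term runs last longer; one range covers both scenarios. The 10 against 15 minute figures are assumptions within that range.
- Alternation puts each scenario under both conditions, so in the between-group comparison scenario length is only partly confounded with leader status. The Statistics section mentions four teams; a 2:2 split would give (330 + 330 + 495 + 495)/4 − (315 + 315 + 210 + 210)/4 = 412.5 − 262.5 = 150 s. Each same-person comparison would still pair a term run with a preterm run.
- The information is not lost. The room camera covers the whole simulation, so run duration can be derived and seconds converted.
- The study is exploratory, and its stated primary outcome is a proportion of participants with changed attention. No confirmatory decision rests on this row.

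A reader might also infer that the table prescribes raw totals of eye movements, which would grow with run length. It does not: those rows ask for a mean and variability without saying of what, and a mean duration or amplitude need not depend on run length.

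**Conclusion.** The unit in Table S2 does not match the scale on which the study was sized, and with unfixed run lengths the tabulated contrast depends on duration as well as on attention. If term runs take 15 min and preterm runs 10 min, one true 20-point effect appears as 105 s or 195 s, according to which teams were led in which scenario. If length differs wholly by leader status, the effect shrinks to 15 s, or equal shares of 35% show as 105 s. Random variation in length costs precision only.

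A reader might conclude that run length can fully cancel or fully reproduce the planned effect. The stated range does not support this. Exact cancellation needs a length ratio of 1.57 (15.7 against 10 min), just beyond the nominal 1.5. The spurious 105 s at a 35% share is below the 120 to 180 s of a true effect at equal lengths. The opposite extreme, 495 − 210 = 285 s, more than doubles the effect only against the 10-minute reference: 285/120 = 2.4, but 285/150 = 1.9 and 285/180 = 1.6. The change is worth making because it is cheap and puts the result on the planning scale.

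**What to change.** Change the Table S2 row to time on each area of interest as a percentage of recorded run time, measured between the same start and end events in every run of both scenarios. Common events are needed because the room camera starts just before the simulation and stops after it. Valid gaze time may serve as the denominator if the eye-tracker output provides it; the protocol does not list it as recorded. Take run duration from the existing recordings, report it per run, and keep seconds beside it as a descriptive line. If saccades, fixations or smooth pursuits are reported as counts, give them per minute of recording.

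The cost is the definition of two events and a small amount of extra data derivation. No new measurement, participant or run is needed.

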## **Simulation**

Prior to each simulation, participants will receive briefing about features of simulation dolls (i.e., to mimic the patient), how they need to assess the doll, and what information they need to obtain from the simulation instructors. Before each scenario each team will have approximately five minutes to prepare for the simulation. We will have two scenarios, one with management of an extreme preterm infant and another with the management of a term newborn with complications at delivery. Details of term and preterm resuscitation scenarios are provided in Appendix-1 and Appendix-2. Both these scenarios were used previously in our neonatal unit simulations. Both the simulation scenarios will need endotracheal intubation with the term baby scenario needing chest compression and umbilical vein administration of epinephrine. We will use the SimNewB (Laerdal Medical, Laerdal, Stavanger, Norway) low

HUFIN\_V5\_March 2022 IRAS: 314695 10

fidelity manikin for term and Premature infant Anne-low fidelity (Laerdal Medical, Laerdal, Stavanger, Norway) for the preterm scenarios, respectively. The two scenarios will be the same for all participants. We will run the two simulation scenarios with three different teams, giving a total of 6 scenarios. Each scenario will be running approximately for 10-15 minutes.

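### The protocol gives both three and four teams; with three, the promised leader-by-scenario balance is impossible and 1 residual degree of freedom remains if team and scenario are both fitted

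*Protocol*

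**What the plan says.** The Simulation section of the Protocol states "We will run the two simulation scenarios with three different teams, giving a total of 6 scenarios", and the Study algorithm section repeats it: "With 3 teams, there will be total of 6 simulation experiments". The layout is crossed: "Each team will undergo one scenario with a team leader and another scenario without a team leader". Leader status alternates from team to team, and of this the protocol says "This will ensure that both scenarios have an equal number of scenarios with and without a team leader".

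The Sample size section takes its control value from an earlier eye-tracking study ("In this study operator spent 35% (SD 8) of time focused on the infant"). It targets 55% with 80% power and alpha 0.05, and arrives at 6 scenarios, 3 per group, and 18 participants.

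The Statistics section has other numbers. It plans summaries with "means, and ranges will be used here based on the number of participants stratified across 4 teams", anticipates 24 participants, and says that this dataset will help to "detect impact of a team lead with a standardised checklist". The named test is the independent t-test, and the work is called exploratory. Table S2 also plans a within-team comparison of the same person.

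**The concern.** Leader status is set once per run, so the leader effect is estimated from as many independent values as there are runs: 6 with three teams, 8 with four. Tracking more members in a run adds no degrees of freedom for this effect.

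The layout has two other sources of variation that the leader comparison should be freed from. One is the team. The other is the scenario: only the term scenario calls for chest compression and umbilical epinephrine, so gaze is likely to differ between scenarios whatever the leader does. With three teams there is very little information left once both are removed, and an odd number of teams defeats the balance that alternation was meant to give. The conflict over team count is therefore more than editorial. It decides whether the balance statement can be true and how much the study can say about its main comparison.

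**Working it through.** **Inputs**
- Teams: 3 (Simulation, Study algorithm) or 4 (Statistics); two runs per team, one with and one without a leader, on different scenarios.
- SD 8, means 35% and 55%, so a difference of 20 points; power 80%, alpha 0.05 (Sample size). Sidedness is not stated. Two-sided is assumed, because the Introduction hypothesises a difference.
- Correlation rho between a team's two runs: not in the document; assumed 0 to 0.9. SD 8 is taken as the SD of a run-level value in either condition.

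**1. The plan's own figure.** Normal approximation: n per group = 2 × (1.960 + 0.842)² × (8/20)² = 2.51, rounded up to 3. The stated 3 per group reproduces. With 3 values per group, however, the two-sided t-test (4 df) has 64% power; 4 per group would have 84%. A one-sided t-test at 0.05 with 3 per group would have 80%, but the protocol does not say that one is intended.

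**2. Balance.** With three alternating teams, one scenario has 2 runs with a leader and 1 without, and the other has 1 and 2. Let P and T be the scenario means, with P the scenario that has two leader runs. The unadjusted leader difference equals the leader effect plus (2P + T)/3 − (P + 2T)/3 = (P − T)/3. Every 3 points of difference between scenarios shifts the unadjusted contrast by 1 point. With four teams, two per sequence, the split is 2:2 and this term vanishes.

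**3. Residual degrees of freedom with fixed team, scenario and leader terms**
- Three teams: 6 − (3 + 1 + 1) = 1; t = 12.706.
- Four teams: 8 − (4 + 1 + 1) = 2; t = 4.303.

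**4. Nominal precision in that model.** SE = ½ × SDdiff × √(1/nA + 1/nB), where SDdiff = 8√(2(1 − rho)) and nA, nB are the teams per sequence. This gives SE = 8√(0.75(1 − rho)) for a 2:1 split and 8√(0.50(1 − rho)) for 2:2. Half-width = t × SE.

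| rho | 3 teams: SE | half-width | power for 20 points | 4 teams: SE | half-width | power for 20 points |
|---|---|---|---|---|---|---|
| 0 | 6.93 | 88.0 | 18% | 5.66 | 24.3 | 48% |
| 0.5 | 4.90 | 62.2 | 25% | 4.00 | 17.2 | 72% |
| 0.75 | 3.46 | 44.0 | 35% | 2.83 | 12.2 | 92% |
| 0.9 | 2.19 | 27.8 | 53% | 1.79 | 7.7 | over 99% |

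At any common rho the three-team interval is (12.706 × √0.75)/(4.303 × √0.50) = 3.6 times as wide. It exceeds the 20-point target unless rho is above about 0.95. The four-team interval falls below 20 points once rho exceeds about 0.32.

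**5. Simpler models with three teams**
- Independent t-test, 4 df: 2.776 × 8 × √(2/3) = 18.1 points. Ignores team and scenario.
- Paired by team, no scenario term, 2 df: 4.303 × 8 × √(2(1 − rho)/3) = 28.1 points at rho 0 and 19.9 at rho 0.5. Keeps the (P − T)/3 shift.
- Scenario but no team, 3 df: 3.182 × 8 × √0.75 = 22.0 points. Ignores the correlation within teams.

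**The case against.** The protocol nowhere prescribes a model with fixed team and scenario terms. It plans descriptive statistics with exploratory t-tests, calls itself a pilot, and a statistical analysis plan that is not shown may say more. Paired analysis fits the crossed layout and still has 2 df. This stands: the 1-df result is conditional on fitting both terms, and a reader who inferred that no within-team analysis of three teams can give a test or an interval would go too far.

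The half-widths depend on a correlation that the document does not give, so no single pair of values, such as 62 against 17 points at rho 0.5, can be presented as fact. The upper end is also harsh. If rho were truly 0, team terms would be unnecessary, and the scenario-only model would give about 22 points with three teams and 14.5 with four. That too stands, although the analyst will not know rho in advance. Further, the half-widths are t times the true SE. With 1 df the realised interval varies widely; at rho 0.5 its median half-width is about 0.674 × 62.2 = 42 points.

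A reader might also infer that significance could then arise only from an implausible effect. It could not be ruled out for a plausible one: at rho 0.5 a true 20-point effect would reach p < 0.05 about 25% of the time. That is low power, not impossibility.

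Finally, the phrase about detecting an impact is attached to 24 participants, in the paragraph that names four teams; it is not claimed for three. Nor does 24 confirm four teams. At four members per team (Participants section), three teams are 12 people and four are 16, while 24 = 6 runs × 4 members. An unfilled group count in the same paragraph suggests that some of its text is left over.

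**Conclusion.** The point holds in a limited form. Two parts need no assumption: the team count conflicts between sections, and with three teams the equal-balance statement is false, so that an unadjusted leader difference contains one third of the difference between scenarios. The degrees of freedom (1 against 2) are exact, given fixed team and scenario terms. The half-widths of about 88 to 28 points with three teams and 24 to 8 with four rest on SD 8 and an assumed correlation of 0 to 0.9; power for 20 points is about 18% to 25% against 48% to 72% for correlations of 0 to 0.5.

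The stated 80% power is not delivered by the planned test if it is two-sided (64%). Nor should a reader conclude that four teams cure the problem: within the adjusted model, power is still below 80% at a correlation of 0.5. Four teams restore the balance and narrow the interval considerably; they do not assure the target power.

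**What to change.** Reconcile the Simulation, Study algorithm, Sample size and Statistics sections to one team count, with participant numbers (18 and 24) that follow from it.

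- **If three teams are kept:** correct the balance statement in the Study algorithm section to a 2:1 split; withdraw the 80% power or restate it with its test and sidedness; report the leader contrast as the three within-team differences, each labelled by scenario, without a confirmatory test; and remove the claim to "detect impact of a team lead with a standardised checklist". The cost is wording only.
- **If four teams are intended:** assign two per sequence, analyse within team with scenario accounted for, and give the expected precision as a range over the assumed correlation (nominally about 24 to 8 points for 0 to 0.9), noting that 80% power is not assured. Relative to the three-team text, the cost is one further session of two runs and four staff.
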